## Abstract

**Background:** Degenerative lumbar spinal stenosis is a prevalent condition in adults over the age of 65 and often leads to deconditioning. Although the benefits of surgery outweigh those of conservative approaches, physical rehabilitation may be used to improve function and to minimize the risk of persistent dysfunction. This study protocol was designed to establish the feasibility of a full-scale randomized controlled trial and to assess the efficacy of an active preoperative intervention program on the improvement of clinical parameters and functional physical capacity in patients undergoing surgery for lumbar spinal stenosis.

**Methods/Design:** Forty patients will be recruited and randomly allocated to one of the 2 treatment arms: 6 weeks supervised preoperative rehabilitation program (experimental group) or hospital standard preoperative management (control group). The intervention group will be trained three times per week, with each session aiming to improve strength, muscular endurance, spinal stabilization and cardiovascular fitness. Intensity and complexity of exercises will be gradually increased throughout the sessions, depending on each participant's individual progress. Primary outcomes are level of low back disability and level of pain. Secondary outcomes include the use of pain medication, quality of life, patient's global impression of change, lumbar extensor muscles endurance, maximum voluntary contraction of lumbar flexor and extensor muscles, maximum voluntary contraction of knee extensors, active lumbar ranges of motion, walking abilities, and cardiovascular capacity. Both the primary and secondary outcomes will be measured at baseline, at the end of the training program (6 weeks after baseline evaluation for control participants), and at 6 weeks, 3 and 6 months postoperatively.

**Discussion:** This study will inform the design of a future large-scale trial. Improvements of physical performances before undergoing lumbar surgery may limit functional limitations occurring after a surgical intervention. Results of this study will provide opportunity to efficiently improve spinal care and advance our knowledge of favorable preoperative strategies to optimize postoperative recovery.

**Trial registration:** US National Institutes of Health Clinical Trials registry NCT02258672, 10 February 2014.

**Keywords:** Prehabilitation, Exercise therapy, Lumbar spine, Spinal stenosis, Surgery

\* Correspondence: [contact]

## Background

Lumbar spinal stenosis (LSS) is one of the most frequent degenerative conditions in older-aged patients [1] and the most common indication for spine surgery in patients older than 65 years [2]. Although several treatment approaches have been suggested in the literature, there is an increasing body of evidence in favor of surgery-related treatment for the management of LSS [3]. For instance, recent evidence shows that decompressive laminectomy/laminotomy alone or combined with fusion for LSS outweighs the effects of non-surgical interventions [3]. In spite of advances in surgical techniques, outcomes following spine surgery are highly variable and advantages following spinal stenosis surgery seem to diminish over time with outcomes becoming similar to those of conservative management at 5 years postoperatively [4]. Furthermore, the frequency of spinal stenosis complex surgeries has increased in the recent years and has been associated with increased costs, risks of complications and resource use, and lower success rates [5, 6].

Although the benefits of surgery outweigh those of conservative approaches for patients with LSS, physical rehabilitation may be used to improve function and to minimize the risk of persistent dysfunction. In fact, a limited course of active physical therapy is initially recommended for patients with LSS [7]. Such a decision may be motivated by the fact that watchful waiting of LSS does not result in catastrophic progressions of neurologic deficits [3]. In addition, there is low-quality evidence suggesting that exercise therapy leads to better short-term outcomes than no exercise with respect to disability, back and leg pain [8]. However, the current scientific knowledge does not provide sufficient evidence to establish clear recommendation for or against the use of physical therapy or exercise as stand-alone treatments for degenerative LSS [7]. Beyond the effectiveness as stand-alone treatments lies the potential adjuvant effects of conservative modalities to surgical outcomes, which are, however, not clearly understood.

On the other hand, the effects of postoperative rehabilitation following lumbar surgery have been extensively studied and yielded optimistic perspectives to improve patients' recovery. A recent systematic review investigated whether active rehabilitation programs following primary surgery for LSS have an impact on functional outcomes and whether such programs are superior to "usual" postoperative care [9]. The study suggests that active rehabilitation is more effective than usual care in improving both short-term and long-term functional status and back and leg pain in adults who underwent spinal decompressive surgery (with or without fusion) for the first time [9].

Although improvements in pain and disability following spine rehabilitation programs have been described in the early postoperative phase, preoperative muscle dysfunctions such as decreased trunk muscle strength and imbalances between trunk extensor and flexor muscles have been reported up to 3 months after surgical fusion [10]. Furthermore, surgical interventions and techniques are known to entail varying levels of invasiveness which can objectively be measured by the levels of biochemical markers of systemic inflammatory response and muscle damage [11]. Such changes will potentially affect muscle function and recovery following surgery. Overall, these results suggest that surgery mostly decreases pain and gross disability but does not systematically lead to improved muscle conditioning. Characterization of postoperative physical capacity deficits should inform the development of targeted approaches aimed at developing improved pain coping and pain-avoidance mechanisms, whilst simultaneously improving overall physical fitness and function.

Authors do acknowledge that much debate persists on which surgical approach is the most cost-effective and may also offer favorable long-term outcomes [2]. Development of innovative surgical techniques, combined with efforts to optimize perioperative patients' management have increased the focus on improvement of postoperative outcomes. The "fast-track surgery" multimodal approach, which focuses on enhancing recovery and reducing morbidity by optimizing preoperative and postoperative patient management, has shown to effectively enhance recovery and reduce need for hospitalization while keeping readmission rates unchanged [12, 13]. Similarly, patient activation, defined as one's propensity to engage in positive health, has been identified as an important modifier of the recovery process, leading to better outcomes and increased compliance to physical therapy after lumbar surgery [14]. Santa Mina et al. recently conducted a systematic review investigating the effectiveness of total-body and region-specific prehabilitation interventions for patients awaiting hip or knee arthroplasty, amongst other conditions [13]. The authors reported improved physical function at the preoperative assessment and improved physical function, length of hospital stay, pain and quality of life following surgery, compared with standard care. We conducted a scoping review exploring current practices in perioperative rehabilitation for lumbar spine surgery and identified only one randomized control trial investigating the effects of a preadaptation program. The study, by Nielsen et al., compared the impact of an integrative program of care, combining both preadaptation and early postoperative rehabilitation, to routine procedures for patients undergoing elective surgery for degenerative disease [15]. Despite the reported improvements in postoperative

function, recovery and hospital stay, the pragmatic design of the study does not allow to tease out the effectiveness of individual interventions.

The Nielson study results, coupled with the positive preliminary results, reported in favor of rehabilitation programs before knee and hip arthroplasty [16–19] has triggered the following question: would the implementation of a preoperative rehabilitation protocol specifically designed for the lumbar region improve the outcomes of surgical interventions? Consequently, the main purpose of the proposed research protocol is to determine the feasibility of conducting a full-scale, randomized controlled trial of prehabilitation versus usual care, and to estimate treatment effects on the improvement of patients' postoperative clinical and functional status.

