## Methods/Design

### Design

This study is a randomized controlled pilot clinical trial. It is design to assess the feasibility and efficacy of an active preadaptation programme in improving patients' recovery following a LSS surgery. The primary outcomes are level of low back disability (as measured by the Oswestry Disability Index (ODI) version 2.1a) and level of pain as measured by a Numerical Rating Scale (NRS)). The proposed study protocol has been approved by the institutional review boards of the *Université du Québec à Trois-Rivières* and *Centre de Santé et de Services Sociaux de Trois-Rivières* (CÉR-2014-008-00), where the study will take place. The trial has been registered with the US National Institutes of Health Clinical Trials registry (NCT02258672). Informed written consent will be obtained from each participant before any intervention is initiated.

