### Measures of feasibility

Full-scale trial feasibility will be assessed by recruitment rate (and reasons for non-participation) and attrition rate, adherence to the protocol and safety of the intervention. Adherence to the prehabilitation protocol will be monitored through the kinesiologist's logbook. For every participant, date of encounter and exercises

[figure not shown]

**Fig. 1** Progression of squat exercise

**Table 1** Schedule of interventions and outcome measures

| Time point                                 | Location          | Data collection                                      |
|--------------------------------------------|-------------------|------------------------------------------------------|
| Baseline assessment                        | In clinic (UQTR)  | Questionnaires a
Physical measurements |
| 6 weeks prehabilitation                    | In clinic (UQTR)  | Physical fitness evolution                           |
| Post-intervention, Preoperative assessment | In clinic (UQTR)  | Questionnaires
Physical measurements              |
| Surgery                                    | Hospital (CSSSTR) | Perioperative data b                      |
| 6-week follow-up                           | In clinic (UQTR)  | Questionnaires
Physical measurements              |
| 3-month follow-up                          | Mailing           | Questionnaires c                          |
| 6-month follow-up                          | Mailing           | Questionnaires c                          |

aQuestionnaires include NRS, ODI, EQ-5D-3 L, Tampa Scale of Kinesiophobia, and BDI

bPerioperative data refers to blood loss, length of surgery and intraoperative complications

cIn addition to the regular questionnaire packet, a home-made questionnaire regarding physical activities undertaken during the postoperative phase will be mailed to the participants

BDI Beck Disability Index, CSSSTR Centre de Santé et de Services Sociaux de Trois-Rivières, EQ-5D-3 L EuroQol-5D-3 L, ODI Oswestry Disability Index, NRS Numerical Rating Scale, UQTR Université du Québec à Trois-Rivières

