### Primary outcome measures

#### Back and leg pain

Pain intensity will be assessed using an 11-point NRS. Each patient will subjectively rate their current level of leg and back pain on a scale of 0 to 10 (0 being an absence of pain 10 being the worst pain imaginable) [21].

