### **Statistical analysis**

Participants' characteristics will be summarized using descriptive statistics (mean, standard deviation). The equivalence of groups at baseline in terms of demographic and clinical variables will be assessed using independent samples *t* tests for continuous variables and chi-square tests for categorical variables. Following an intention-to-treat principle, estimates of efficacy (Group and Time main effect, as well as Group x Time interactions) will be analyzed using a repeated-measure analysis of variance (ANOVA). The statistical significance level will be set at 5 % and missing data will be analyzed using multiple imputation methods.

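### The purpose is feasibility plus effect estimation, but the only primary outcomes are three unranked efficacy scores tested at 5% in a sample not sized for testing

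*Protocol*

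**What the plan says.** - **Purpose.** The Background gives two aims in one sentence: "the main purpose of the proposed research protocol is to determine the feasibility of conducting a full-scale, randomized controlled trial" of prehabilitation against usual care, "and to estimate treatment effects on the improvement of patients' postoperative clinical and functional status". The Design section is broader: "It is design to assess the feasibility and efficacy of an active preadaptation programme in improving patients' recovery following a LSS surgery".
- **Primary outcomes.** Design: "The primary outcomes are level of low back disability (as measured by the Oswestry Disability Index (ODI) version 2.1a) and level of pain". Under Back and leg pain, each patient rates the "current level of leg and back pain on a scale of 0 to 10". No rule combines the two ratings or ranks one above the other, so there are three primary scores. No feasibility measure is called primary or secondary.
- **Timing.** The Abstract lists baseline, the end of the training period, and 6 weeks, 3 months and 6 months after surgery. No visit is named as primary.
- **Analysis.** Under Statistical analysis, efficacy is assessed by repeated-measures ANOVA for Group, Time and Group x Time. "The statistical significance level will be set at 5" per cent. Feasibility is not mentioned there.
- **Sample size.** The number is attributed to time constraints, the local surgery rate and a guideline of 10 to 20 per group for estimating variance and informing feasibility. No effect size, SD or power is given.
- **Feasibility.** "Full-scale trial feasibility will be assessed by recruitment rate (and reasons for non-participation) and attrition rate", together with adherence and safety. No value is given that would count as feasible.

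**The concern.** The outcome hierarchy and the analysis do not follow from the purpose. One half of the purpose, feasibility, has measures but no place among the primary outcomes and no limit against which to judge them. The other half, estimation, is given significance tests on three unranked scores.

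The sample was chosen to inform feasibility and estimate variance. If efficacy is then read from p-values, two errors are open. A null result may be taken as evidence that prehabilitation does not work when the trial could not have shown a moderate benefit. Or one score below 0.05 out of three may be reported as efficacy, with nothing fixed beforehand to say which score or visit counts. Meanwhile the measures that bear on whether a full trial is practicable would be interpreted without any limit set in advance.

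**Working it through.** **The plan's own figure.** There is no power calculation to reproduce. The only check available is 2 x 20 = 40: the upper end of the 10 to 20 per group guideline gives the planned total if allocation is 1:1. The ratio is not stated.

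**Inputs from the protocol.** Three primary scores (ODI, leg pain, back pain); five assessments; Group and Group x Time effects; 5% level; 40 patients.

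**Assumptions.** Two-sided tests; 20 per arm; correlation between scores 0.3 to 0.7; effects of 0.3, 0.5 and 0.8 SD. The documents give none of these.

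**1. Chance of at least one p<0.05 with no true effect**

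For k independent tests it is 1 - 0.95^k. Correlation between scores lowers it, so the correlated values were simulated. Group was treated as a normal test and Group x Time as a chi-square test on 4 df (five visits, two groups). The Time main effect is left out because it does not compare the groups.

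| Tests counted | Independent | Score correlation 0.7 to 0.3 |
|---|---|---|
| One per score (k = 3) | 1 - 0.95^3 = 14.3% | about 11% to 13-14% |
| Group and Group x Time per score (k = 6) | 1 - 0.95^6 = 26.5% | about 21% to 25% |

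The range is therefore about 11-14% for three tests and 21-26% for six, against a nominal 5%.

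**2. Power of one two-group comparison, 20 per arm**

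Non-central t with 38 df and noncentrality d x sqrt(20/2):

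| Assumed effect d | Noncentrality | Power at 5% |
|---|---|---|
| 0.3 SD | 0.95 | 15% |
| 0.5 SD | 1.58 | 34% |
| 0.8 SD | 2.53 | 69% |

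Power reaches 80% only at about 0.91 SD.

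**3. What the sample can give as an estimate**

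The 95% CI half-width for a difference in means is t(0.975; 38) x sqrt(2/20) = 2.024 x 0.316 = 0.64 SD. That is wide, but it is reportable and useful for planning.

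**4. Precision of the feasibility measures**

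Exact (Clopper-Pearson) 95% intervals for illustrative counts: 32/40 retained = 80% (64% to 91%); 16/20 adherent in the trained arm = 80% (56% to 94%). A limit chosen after seeing intervals this wide could be placed to support either conclusion.

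**The case against.** **The purpose is dual.** ODI and pain serve the second aim directly, so it would be wrong to say that the primary outcomes have nothing to do with the objective. This stands. What remains is that feasibility is not ranked among the primary outcomes, and that an aim worded as estimation is given a significance level.

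**Nothing ties the go/no-go decision to p-values.** A reader might infer that the pilot's conclusion would rest on p<0.05. The protocol does not say so. Its feasibility section judges a full trial by recruitment, attrition, adherence and safety, and the Discussion calls the results preliminary. The 5% level is only the sole numerical criterion stated for any outcome.

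**The tests should not be over-counted.** A reader might multiply three scores by four post-baseline visits to get twelve tests. No section plans tests at each visit; the ANOVA gives omnibus effects per score. Three to six is the supported count.

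**Low power depends on the assumed effect.** A reader might infer that the trial would usually miss a real effect. That is true at 0.5 SD but not at 0.8 SD, where power is about 69%. The planned model also uses repeated measurements, which the simple comparison ignores. The protocol claims no power.

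**Some of this belongs in a statistical analysis plan.** Multiplicity handling and the method for analysing feasibility rates may well be there, and their absence here is not criticised. The choice of primary outcomes and the 5% level are fixed in the protocol itself.

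**Conclusion.** The point holds as a mismatch within the protocol. A study meant to determine feasibility and estimate effects, and sized only for that, makes three unranked efficacy scores its sole primary outcomes and assesses them at 5% with no lead score or visit. The feasibility measures are left outside the primary tier, without progression limits.

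The inflation of the false-positive risk is moderate: two to five times the nominal 5%, depending on whether three or six tests are counted. The limits on power and precision in the working depend on the assumed allocation, effect sizes and simple comparison.

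The missing limits would be a minor matter alone. They matter here because the analysis is pointed at efficacy testing instead. The change is worth making, but nothing here invalidates the trial or its data.

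**What to change.** 1. Make recruitment, attrition, adherence and safety the primary outcomes. Report the proportions with exact 95% CIs against progression limits that the sponsor sets before looking at the data. The limits should allow for the interval widths shown above.
2. For adherence, record sessions offered as well as sessions attended. The nominal schedule is 3 x 6 = 18 sessions, but Ethical considerations says the training period may vary between patients. The logbook is described as recording encounters and exercises performed, so a denominator has to be added.
3. Name one post-operative visit in advance, and make the between-group ODI difference at that visit the lead clinical estimate.
4. Report that difference and the leg and back pain differences with 95% CIs, as estimates for planning the full trial. Make no efficacy claim from p<0.05.

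**Cost.** Mostly protocol wording. The outcome scores and the feasibility measures are already planned; the one addition is the record of sessions offered. The downside is that the pilot gives up a headline efficacy test.

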## Methods/Design

### Design

This study is a randomized controlled pilot clinical trial. It is design to assess the feasibility and efficacy of an active preadaptation programme in improving patients' recovery following a LSS surgery. The primary outcomes are level of low back disability (as measured by the Oswestry Disability Index (ODI) version 2.1a) and level of pain as measured by a Numerical Rating Scale (NRS)). The proposed study protocol has been approved by the institutional review boards of the *Université du Québec à Trois-Rivières* and *Centre de Santé et de Services Sociaux de Trois-Rivières* (CÉR-2014-008-00), where the study will take place. The trial has been registered with the US National Institutes of Health Clinical Trials registry (NCT02258672). Informed written consent will be obtained from each participant before any intervention is initiated.

### Recruitment

Participants will be recruited at the *Centre de Santé et de Services Sociaux de Trois-Rivières* during their encounter with their treating neurosurgeon once the decision has been made to move forward with a surgical intervention. If deemed eligible, patients willing to participate in the study will be provided with an overview of the study purpose and content and they will be asked permission to be contacted by the research team. Further details will be given over the phone by a member of the research team and an assessment date will be set for the participant. Participants will be guided through the informed consent process and baseline demographics and physical measures will be collected. At the end of the initial assessment visit, a member of the research team will open the sealed envelope to randomly allocate participants to one of the two groups (intervention versus control). Treatments will be schedule after randomization for participants in the intervention group.

### Eligibility criteria

The inclusion criteria for study subjects are: having a clinical history and diagnostic imaging evidence of LSS, being over 18 years, having degenerative LSS affecting one or multiple vertebral levels, awaiting LSS surgery (minimally invasive or open approach), and being able to provide written informed consent voluntarily. The exclusion criteria are: non-degenerative LSS, presence of inflammatory arthritic conditions, altered cognitive capacities, and vertebral instability requiring non-instrumental or instrumented fusion, and individuals deemed ineligible by their treating neurosurgeon and those unable to comprehend or express themselves in French.

